#### Aim-1 Formative Insights

In the course of exploratory and interim analyses of baseline and daily diary data, a range of environmental stressors with salience to the everyday lives of New Orleans area people living with HIV emerged. The study’s original objective was to understand how local spatial exposure and daily experiences may serve as determinants of traumatic stress or retraumatization connected to downstream maladaptive coping behaviors such as alcohol use and consequent patterns of ART nonadherence [79,80]. Our preliminary analyses did not find associations between outcomes related to alcohol use and daily mood across activity path–based spatial alcohol and violence exposure. These null results necessitated a departure from the original aim-1 goal of building generalizable place-based exposures as just-in-time adaptive intervention (JITAI) inputs into the NOLA GEM app. As such, tailoring variables, and the daily diary items through which they were captured in aim 1, were selected based on their overall prevalence at baseline, capturing past and cumulative experiences and associations with key outcomes within individuals on a given day among aim-1 participants. In recognition of the irreducibly idiographic nature of spatial traumatic stress determinants evidenced in this study, an individually customizable geofencing solution was built into the eventual NOLA GEM app (detailed in the *NOLA GEM App* section).

These stressors, with relevant statistics illustrating the rationale for their inclusion as JITAI tailoring variables, are provided in Table 2.

**Table 2 table2:** NOLA GEM app just-in-time adaptive intervention tailoring variables—description and rationale.

Stressor	Rationale	Sample item or items^a^
Mental health challenges	51.22% endorsed “somewhat” or “very” stressful mental health challenges (past 30 days)^b^	In the past 30 days, how stressful were the following events? You can say “Not Applicable” if you did not experience this event. Worried about my mental health (not at all, somewhat, a lot)

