### Aim 3: Acceptability, Feasibility, and Preliminary Efficacy

#### Trial Design

The pilot trial will be a single-blind parallel superiority trial assessing NOLA GEM (treatment arm) against GEMA alone (control arm) for a period of 21 days, allocated at a 1:1 ratio. In contrast to aim 1, the NOLA GEM app is capable of delivering SMS text message–linked daily diaries and recording GPS coordinates without recourse to third-party software. The GEMA-alone control was chosen to control for any intervention effects of recording daily mood, experiences, and other psychosocial variables as some research has demonstrated improvements in outcomes such as PTSD, depressive symptoms, and emotional awareness in participants recording their experiences using EMA methods [112-115] (aim-2 interviewees, unprompted, disclosed similar enhancements in self-awareness during their experience as aim-1 participants). This design establishes a high-resolution comparator to NOLA GEM, capturing GEMA data across both trial arms while potentially isolating the effects of JITAI-based momentary provision of LIFT content as a hypothesized mechanism of action.

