##### ART Adherence

The capacity to maintain ART regimens will be assessed using a novel single-item visual analog scale (VAS) [72]. The VAS asks participants to estimate the percentage of their medication that they have taken in the past 30 days. Details of the VAS format and development are provided by Giordano et al [121]. In addition, daily diary measures operationalizing use of and feelings toward ART medication will be administered over the 21-day trial period (eg, “Did you have difficulty fitting your HIV treatment into your daily routine yesterday [Yes/No]”). These measures are provided in full in Multimedia Appendix 3.

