#### Analytic Approach

Consistent with aim 1, aim-3 data will be cleaned and saved in SAS data files (SAS Institute), with extensive consistency checks conducted at all levels of data [66]. At the completion of each check, the data will be added to the existing database for analysis. GPS data will be stored on a password-protected server and constructed into activity paths, replicating the aim-1 approach [66].

Preliminarily, descriptive and crude bivariate associations between variables of interest will be generated. Daily diary completion rates and agreement with aggregate retrospective survey data for comparable measures will be calculated. Data reduction techniques, mitigating the high volume and dimensionality of GEMA-derived data, will include the creation of composite indexes of cumulative risk, with exploratory factor analysis, assessment of internal consistency, and Bonferroni correction applied as warranted.

Aim-3 analyses of preliminary efficacy will include analysis of each day-to-day distal outcome as a continuous variable as well as average exposures across the total intervention period. We will explore potential transformations to approach normality on key response variables [133]. Linear mixed-effects models will relate day-level outcomes to day-level indexes of cumulative risk and protective exposure derived originally from aim 1, adjusted for baseline values [134]. Random effects will be included to account for within-subject series correlations. Control variables will be modeled as fixed effects.

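### The one model named for preliminary efficacy has no randomised-arm term and does not fit the primary HIV care outcomes, so as stated it does not estimate NOLA GEM versus GEMA alone

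*Protocol article*

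**What the plan says.** Trial Design describes a randomised comparison: "The pilot trial will be a single-blind parallel superiority trial assessing NOLA GEM (treatment arm) against GEMA alone (control arm", with equal allocation over 21 days. Study Objectives (aim 3) asks for preliminary efficacy relative to GEMA alone on care engagement, ART adherence and viral suppression. Limitations warns that the choice of control may inflate the preliminary efficacy estimates on the primary outcomes, so an estimate against that control is expected.

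The efficacy paragraph of Analytic Approach begins: "Aim-3 analyses of preliminary efficacy will include analysis of each day-to-day distal outcome as a continuous variable as well as average exposures across the total", meaning the whole 21-day period. The model is then given: "Linear mixed-effects models will relate day-level outcomes to day-level indexes of cumulative risk and protective exposure derived originally from aim 1". It also carries a baseline adjustment. Random effects cover within-person correlation, and the last sentence adds: "Control variables will be modeled as fixed effects". The section also promises descriptive statistics and crude bivariate associations. It does not mention arm, group, allocation or a between-arm comparison.

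**The concern.** The article does not simply leave the efficacy model to another document. It names one, and the predictor of interest in that model is a daily exposure index instead of the randomised assignment. Aim 1 was an observational diary study without an intervention, so an index derived from it cannot stand in for arm.

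An analyst who followed the section literally would report how daily risk and protective exposures go with daily outcomes among all participants. That extends aim 1. It does not use the randomisation, and it supplies no arm effect with an interval to support the planned full-scale trial. The same analyst would also find no stated method for the follow-up measures that define the primary care-continuum outcomes.

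**Working it through.** The protocol gives no effect size, SD, alpha or power for this analysis, so there is no figure to reproduce. The check sets the stated model beside the objective and the outcomes.

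**1. What the stated model estimates.** For person i on day t, with daily index E, baseline value Y0, control variables C and random effects b:

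Y(it) = β0 + β1·E(it) + β2·Y0(i) + γ·C(i) + b(i) + e(it)

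The coefficient of interest is β1, the exposure slope. There is no arm indicator A(i), so no coefficient corresponds to NOLA GEM minus GEMA alone. If arm were meant to be one of the control variables, it would enter as a nuisance term beside E, which raises step 3.

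**2. Whether the primary care-continuum measures fit it.** Primary Outcomes places these at postintervention and at the 30- and 90-day follow-ups.

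| Domain (section) | Measure | Daily continuous series? |
|---|---|---|
| Care Engagement | 12-item self-efficacy scale | No, follow-up scale |
| Care Engagement | Percentage of appointments missed, asked at 90 days | No, one percentage |
| ART Adherence | Visual analog percentage for the previous 30 days | No, follow-up percentage |
| Viral Suppression | Latest viral load below 50 copies/mL, yes or no, at 90 days | No, one binary value |

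None of the four is day-level, and one is binary. In these sections only ART adherence has supplementary diary items. The plan for "analysis of each day-to-day distal outcome as a continuous variable" therefore reaches at most the diary part of one of the three domains.

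**3. Why adding arm to the stated model is not enough.** Under Participants and Procedures, randomisation precedes the baseline visit and app onboarding, so every diary index is measured after allocation. Suppose the total arm effect is Δ and a share m of it acts through the index. With linear effects and no other confounding:

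- outcome on arm plus baseline: arm coefficient = Δ
- outcome on arm, baseline and index: arm coefficient = (1 − m)·Δ

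The documents give no value for m. It could lie anywhere from 0 (nothing lost) to 1 (everything lost). It also depends on what is in the index. Coping and stress items in the diary are things the app tries to change. Alcohol outlet density, tract crime rates and emergency-call data, listed as aim-1 exposures under Geospatial Tracking, need not respond to it.

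**4. What an arm contrast could deliver here.** Sample Size Considerations gives 30 analysed per arm. Assuming one value per person, a common SD and no gain from baseline adjustment, the 95% interval half-width is 1.96 × √(2/30) = 1.96 × 0.258 = 0.51 SD. That is wide, but it is an estimate of the right quantity. It agrees with the statement in Limitations that the pilot is underpowered for formal efficacy testing.

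**The case against.** The best reply is that this is a condensed article about a pilot. Its list of efficacy analyses says what they include and does not claim to be complete. Crude bivariate associations could cover arm, and the comparison with GEMA alone is plainly intended elsewhere. Model terms are commonly left to an analysis plan. Feasibility, acceptability and usability also stand under Primary Outcomes, and they do not depend on this model.

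Much of that stands. A reader might infer that the trial will produce no arm comparison at all; the documents do not support this. Nor does the section say that viral suppression or missed appointments will be forced into the daily model, only that no other model is named. It would also go too far to call every primary measure a single-time-point one, because Primary Outcomes allows some of them to be repeated.

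Three further inferences are tempting and unsupported:

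- *That a set fraction of the effect would be lost.* Any such figure restates an assumed mediation share in a model that the document does not state.
- *That serial correlation is mishandled.* The section promises random effects for within-person correlation and does not restrict them to an intercept. The issue would in any case concern an exposure slope, not the arm effect.
- *That yes/no diary items will be analysed as normal variables.* ART Adherence gives one example item of this type, and composite indexes are planned.

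The reply does not remove the central point. Being a pilot excuses the lack of a powered test but not the lack of an arm estimate. Condensation explains missing detail, but here a model is stated under the efficacy label and it answers another question.

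**Conclusion.** The point holds for the model as stated. Analytic Approach names one preliminary-efficacy model. It has no arm term, and it suits none of the four follow-up measures that operationalise the primary care-continuum outcomes. It therefore does not estimate the comparison that the trial randomises for.

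This is a structural defect and carries no numerical bias figure. The only size that can be attached to adjusting for post-randomisation diary indexes is the range in step 3, from no loss to complete loss, with the true share unknown. The conclusion rests on the wording of this section alone. A fuller analysis plan, if there is one, may already contain the arm contrasts, and then the article and that plan should be made to agree.

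**What to change.** Rewrite the efficacy paragraph of Analytic Approach as arm contrasts, each reported as an estimate with a 95% confidence interval and not as a powered test:

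- **Scale, visual analog and percentage outcomes:** a linear model with arm and the baseline value, where one is collected. Participants and Procedures mentions a baseline assessment without listing its scales, so say which baseline values exist.
- **Viral suppression:** a risk difference or a logistic model by arm.
- **Diary outcomes:** a mixed model with arm, day and arm-by-day, using a link suited to the type of item.

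Move the daily risk and protective exposure models to a part labelled exploratory. Keep diary indexes that are measured after randomisation and that the app could change out of the arm models, since adjusting for them can remove part of the arm effect.

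The cost is one rewritten paragraph and some extra analysis code. No further data collection is needed, because baseline adjustment is asked for only where a baseline value is available.

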### Ethics Approval

All methods and materials were reviewed and approved by the Biomedical and Social Behavioral Institutional Review Boards of Tulane University (aim 1: 860463; aim 2: 2021-1220; and aim 3: 2022-1861).

## Results

Aim 1, enrolling 89 people living with HIV, was completed in September 2022. Aim 2, informed by a pilot aim-1 sample of 49 participants and a subset of 12 interviewees, was completed with the handover of the NOLA GEM app to investigators in April 2022. NOLA GEM is available to aim-3 participants as a native iOS and Android app hosted in the Apple App Store and Google Play Store, respectively. The app’s onboarding and sign-on flow accommodates both intervention (treatment arm) and GEMA-only (control arm) account credentials. Ethics approval was obtained, and recruitment subsequently began, in July 2023. We anticipate that all follow-up appointments will be completed by February 2024, with the final results ready for dissemination by May 2024. The results will be disseminated to key stakeholders via scientific conferences, peer-reviewed academic journals, and Tulane University social media channels. Ultimately, as an R34-supported project, the longer-term objective is to “prune” underused or preliminarily inefficacious JITAI logics to refine a parsimonious NOLA GEM theory of change, consequently supporting an application for National Institutes of Health support for a full-scale RCT.

## Discussion

### Summary

This study aims to advance knowledge on temporally fluctuant and place-based stressors endured by people living with HIV in New Orleans and assess the acceptability, feasibility, and preliminary efficacy of NOLA GEM, a JITAI-consistent mHealth intervention responsive to these stressors. Key to the significance of NOLA GEM is its capacity to capture and intervene in real time on a holistic range of time-variant psychosocial and behavioral variables [10,15,21,60,61] alongside crucial neighborhood-level factors known to affect CoC outcomes and well-being among people living with HIV [11,12,23,44-48], particularly violence-affected people living with HIV [1,4,7,15]. To our knowledge, NOLA GEM is the first smartphone-delivered, trauma-informed intervention tailored for people living with HIV. As such, it will leverage a well-demonstrated EBI [33,34,36-39]; previous research supporting cognitive behavioral touch points for intervention among people living with HIV with trauma histories [135-137]; and the confidentiality, discretion, and real-time accessibility of mHealth [54,86]. Through the latter strengths in particular, we hope to address participant privacy and in-person group attendance concerns that may have stemmed the uptake and, possibly by extension, the longer-term efficacy of *Improving AIDS Care after Trauma* [39], the LIFT adaptation preceding NOLA GEM [38].

Notably, the mean ages of aim-1 and aim-2 participants were 57 and 58 years, respectively. This skew toward older adulthood relative to the intended user base of many people living with HIV–tailored mHealth interventions [138] may have influenced the design of NOLA GEM. Since 2014, smartphone adoption has accelerated among older adults, reaching 86% among adults aged >50 years and 62% among adults aged >70 years [139]. With motivation (both intrinsic and extrinsic) and proper feedback and support, mHealth and eHealth tools can find success among older adults [140], including older people living with HIV who, for example, engaged with the features of the *PositiveLinks* platform in a significantly more dedicated, sustained manner than younger (aged <50 years) users [141]. Success among this user base relies on a baseline degree of digital readiness [140], which is itself often contingent on device familiarity—a strength of NOLA GEM, which leverages common SMS text message and native app functional affordances, distinct from, for example, a wearable actigraphy sensor. Though some aim-2 participants attached their preferred coping techniques to their age (accepting and adapting: “You’re getting older and you can’t do anything about it. Just accept it and let move on” [participant F]), few, when prompted, described personal traits such as age or disability influencing their personal technology use. Post hoc, open-ended usability interviewing conducted during or shortly after intervention offboarding will allow us to examine the role of participant age (among both younger and older adults) qualitatively within the specific context of the NOLA GEM user experience.

Overarchingly, our objective is to introduce an innovative model of adaptive coping support in a periurban US Gulf South context characterized by elevated rates of HIV prevalence [41], poverty and economic inequality [42,43], and violent crime [44], reinforcing a focus on traditional HIV CoC end points with precision-tailored support for person-centered proximal outcomes grounded in the lived experience of local people living with HIV.

### Limitations

As a small-scale pilot trial, aim 3 is subject to a number of inherent limitations. First, and by design [142], it is underpowered to examine efficacy in a formal hypothesis-driven manner. Mediation analyses of proximal outcomes will necessarily be exploratory in nature and inform the causal pathway hypotheses for the planned RCT. Although the selection of control conditions for mHealth trials remains an area of active investigation and debate [143], a passive GEMA-alone control may inflate preliminary estimates of NOLA GEM (incorporating GEMA+LIFT coping skills) efficacy on primary outcomes, an issue that is potentially exacerbated by the small sample size [144]. Adaptations of complex, sequential, and multicomponent group interventions risk dismantling key mechanisms of action that undergird effectiveness in their original contexts [33,34,101]. Adaptation to mHealth across HIV science remains a highly active but often methodologically impromptu area [145]. Pragmatic considerations required us to deprecate certain components of LIFT as originally manualized [33] and demonstrated to reduce traumatic stress [34,36]. Group cohesion and dedicated in-person facilitation of the group member disclosure and support processes define the LIFT intervention trajectory, which is sequenced across 15 sessions [33]. We abstracted the CTSC-based strategies built into NOLA GEM from their original, in-person, session-by-session framework to activate the “just-in-time” aspect of a JITAI adaptation while mitigating ethical concerns that, if faced with an acute stressor, a NOLA GEM user would be denied the best-suited coping support if they had not yet reached the appropriate session had a strictly linear intervention model been retained. Similarly, although a peer-to-peer support forum or social media–style feature [146,147] in which users could interact pseudonymously was briefly considered, lacking active human (vs algorithmic) content moderation, such a space could become consumed with off-topic, inane, or even outrage-inducing user-generated content and external media [86,148]. In addition, by recruiting people living with HIV who were either violence-affected individually or lived in a high-violence neighborhood, a degree of heterogeneity in needs was introduced into the aim-1 and aim-2 samples, which may have swayed the formative insights—and, by extension, intervention design—derived from the *New Orleans Alcohol Use in HIV* study subsamples. Although violence exposure at the within-person and neighborhood levels is associated with distinct sequelae among people living with HIV, it is our intention that the multitude of possible NOLA GEM user journeys can offer the necessary support to a wide range of personal violence histories. By nature, an acceptability and feasibility trial will provide insights on many of these concerns, whereas merged paradata and GEMA data will permit high-resolution analyses of users’ engagement with and navigation of NOLA GEM [149].

### Conclusions

Aligning user-centered development practices with principles that elevate the lived expertise of people living with HIV, mHealth-adapted EBIs can sustain well-specified theories of change while leveraging the affordances of mobile technologies. The results of the aim-3 trial will generate needed evidence concerning the value of such a locally tailored JITAI approach while pointing toward opportunities to improve upon the initial release of NOLA GEM in anticipation of a fully powered RCT offering definitive evidence of the potential of mHealth-delivered effective coping support that operationalizes the self-knowledge of communities of end users.

## Appendix

Multimedia Appendix 1 Aim-1 daily diary measures—domains and operationalization.

Multimedia Appendix 2 Complete NOLA GEM just-in-time adaptive intervention user story maps.

Multimedia Appendix 3 Aim-3 daily diary measures—domains and operationalization.

## Abbreviations

ART: antiretroviral therapy
CoC: continuum of care
CTSC: cognitive theory of stress and coping
DSM-5: Diagnostic and Statistical Manual of Mental Disorders, Fifth Edition
EBI: evidence-based intervention
EMA: ecological momentary assessment
GEMA: geographic ecological momentary assessment
HIPAA: Health Insurance Portability and Accountability Act
JITAI: just-in-time adaptive intervention
LIFT: Living in the Face of Trauma
mHealth: mobile health
PTSD: posttraumatic stress disorder
UX: user experience
RCT: randomized controlled trial
REDCap: Research Electronic Data Capture
SPIRIT: Standard Protocol Items: Recommendation for Interventional Trials
SUD: substance use disorder
VAS: visual analog scale
